### ***Secondary outcome measures***

#### ***Kinematic Measurements***

The lip and tongue function during speech production will be traced real time and objectively measured using the Enhanced Wave Speech Research System (Wave) (Northern Digital Inc., Canada). The Wave uses advanced 3D electromagnetic tracking technology to simultaneously track up to 16 sensors in five degrees of freedom (5 DOF). Movement is tracked in real time within a large 500 mm cubic measurement volume (electromagnetic field) with a sampling rate of 400 Hz. No line of sight is needed between the system and the subject to maintain accurate and reliable dimension and position tracking. The Wave is a non-invasive system and it meets the IEEE standards for electromagnetic radiation for head and torso tracking. The sensors are lightweight, ultra-small and disposable, can be safely attached to the subject using standard medical glue or adhesives and have little impact on articulation during speech production. All participants will be required to produce single-syllable real words of CV construction at high level tone embedded in a carrier phrase and repeat some syllables (i.e., /pa/, /ta/, /ka/ and /pataka/). The displacement, velocity, acceleration and duration of lips and tongue movement during speech production will be analysed.

#### ***Strength and endurance assessment***

The strength and endurance of lip and tongue will be objectively measured using the Iowa Oral Performance Instrument (IOPI). Tongue strength will be assessed by asking the participant to “squeeze as hard as you can” with the anterior dorsum of the tongue against the IOPI tongue bulb placed against the hard palate. Lip strength will be assessed by asking the participant to squeeze their lips as hard as they can against the IOPI bulb placed between the lips. Tongue and lips endurance will be assessed by asking the participant to maintain 50% of maximal pressure (Pmax) as long as possible. Visual feedback will be given using the PicoScope 6 (Pico Technology, UK). The experimenter will provide spirited verbal encouragement throughout the trial. The trials will be timed with a stopwatch.

#### ***Quality of Life measurement:***

The Chinese version of The Quality of Life of the Dysarthric Speaker (QOL-DyS) questionnaire [44] will be used to assess participants’ subjective speech related quality of life. This self-reported questionnaire was adapted by the PI and Co-Is and is currently being validated. It includes 40 items covering four aspects of speech characteristics, functioning and well-being measurement including speech characteristics of the words, situational difficulty, compensatory strategies and perceived reaction of others.

### **Statistical analyses**

Two-way repeated-measures Analyses of Variance (ANOVAs) will be applied for each dependent variable. Post-hoc multiple comparisons will be carried out when necessary.

1. Darley, F.L., A.E. Aronson, and J.R. Brown, *Differential diagnostic patterns of dysarthria*. Journal of Speech and Hearing Research, 1969. **12**: p. 246-269.
2. Duffy, J.R., *Motor speech disorders: Substrates, differential diagnosis, and management*. 3rd ed. 2013, St. Louis, MO: Elsevier Mosby.
3. Mackenzie, C., *Dysarthria in stroke: A narrative review of its description and the outcome of intervention*. International Journal of Speech-Language Pathology, 2011. **13**(2): p. 125-136.
4. Ng, P.W., *The stroke epidemic*. Hong Kong Medical Journal, 2007. **13**: p. 92-94.
5. Woo, J., et al., *Stroke incidence and mortality trends in Hong Kong: Implications for public health education efforts and health resource utilisation*. Hong Kong Medical Journal, 2014. **20**(Supplement 3): p. S24-29.
6. Yorkston, K.M., et al., *Evidence for effectiveness of treatment of loudness, rate, or prosody in dysarthria: A systematic review*. Journal of Medical Speech-Language Pathology, 2007. **15**(2): p. xi-xxxvi.
7. Yorkston, K.M., et al., *Management of motor speech disorders in children and adults*. 2nd ed. 1999, Austin, Texas: Pro-Ed.
8. Wenke, R.J., P. Cornwell, and D.G. Theodoros, *Changes to articulation following LSVT® and traditional dysarthria therapy in non-progressive dysarthria*. International Journal of Speech-Language Pathology, 2010. **12**(3): p. 203-220.
9. Wenke, R.J., D. Theodoros, and P. Cornwell, *The short- and long-term effectiveness of the LSVT® for dysarthria following TBI and stroke*. Brain Injury, 2008. **22**(4): p. 339 - 352.
10. Flöel, A., *Non-invasive brain stimulation and language processing in the healthy brain*. Aphasiology, 2012. **26**(9): p. 1082-1102.
11. Adeyemo, B.O., et al., *Systematic review of parameters of stimulation, clinical trial design characteristics, and motor outcomes in non-invasive brain stimulation in stroke*. Frontiers in Psychiatry, 2012. **3**(88).
12. Kim, D.-Y., et al., *Effect of transcranial direct current stimulation on motor recovery in patients with subacute stroke*. American Journal of Physical Medicine & Rehabilitation, 2010. **89**(11): p. 879-886.

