## **Research plan and methodology**

### **Participants**

Participants will include 60 adults who are at least 6-month after their initial stroke and have suffered a dysarthria post-stroke. Based on the study by You, Chun [38] with an effect size of 1.08, priori power analysis showed that at least a total of 40 participants (20 participants in each group) are needed. Taking into account an attrition rate of around 25%, the minimum sample size for this study is 50 participants. The requirement of 6 months post stroke is to avoid possible spontaneous recovery effect. As sex does not appear to be a factor in the study, both male and female participants will be recruited. Participants will be recruited from Queen Mary Hospital and Tung Wah Hospital. Standard inclusion/ exclusion criteria for speech research and exclusion criteria for tDCS as will be adopted in the proposed study. Individuals with a personal or family history of epilepsy or seizures; a history of a neurological condition, speech disorders, oro-maxillo-facial surgery involving the tongue and/or lip, severe cognitive impairment, severe aphasia, in an unstable or serious medical condition including heart disease, metallic foreign body implant and/or any medications that lower neural thresholds (e.g. tricyclines, antidepressants, neuroleptic agents, etc.) will be excluded from the study. All participants will be screened using Cantonese mini-mental state examination (MMSE) and speech and language screening to exclude patients with cognitive impairment, aphasia and apraxia of speech.

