### ***Study design***

The proposed project will be a randomized, placebo-controlled double-blinded control study. Following recruitment, the participants will be randomly assigned to one of two groups: Group 1 (n = 30) will receive anodal tDCS stimulation and intensive speech and voice therapy; Group 2 (n = 30) will receive sham tDCS stimulation and intensive speech and voice therapy. Both objective and subjective measurements on speech and speech-related physiological function will be administered four times in this study. The data collection will include perceptual and acoustic measurements, kinematic measurements, strength and endurance measurements and dysarthria-related quality of life measurements. The assessment will be conducted prior to tDCS baseline, immediately post tDCS, and post tDCS at 1-month and 3-month to assess the treatment outcome.

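### The repeated-measures ANOVA fixed in the protocol makes baseline an outcome level, tests a 3-df omnibus interaction and in its classical form uses completers only; a baseline-adjusted mixed model would answer the aim directly

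*Protocol*

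**What the plan says.** Protocol, Statistical analyses, consists of two sentences: "Two-way repeated-measures Analyses of Variance (ANOVAs) will be applied for each dependent variable" and "Post-hoc multiple comparisons will be carried out when necessary". The factors of the ANOVA are not written out.

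Study design randomises participants to two groups of 30 and gives the schedule: "The assessment will be conducted prior to tDCS baseline, immediately post tDCS, and post tDCS at 1-month and 3-month to assess the treatment outcome". Baseline is therefore one of the four measurement occasions.

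Participants states "Participants will include 60 adults", a planning value "with an effect size of 1.08", a requirement that "at least a total of 40 participants (20 participants in each group) are needed", and then "Taking into account an attrition rate of around 25%, the minimum sample size for this study is 50 participants". Significance level, sidedness and power are not given there.

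The goal section sets out to examine both short-term and long-term effects of stimulation.

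**The concern.** The protocol does more than leave detail open: it names a method, and a later analysis plan would inherit it. Read with the schedule, that method has three costs.

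- **Baseline is an outcome level.** Randomisation makes a treatment effect at that visit impossible, yet the visit enters the test as one of four levels and is not used as a covariate to reduce residual variance.
- **The test is an omnibus one.** The group-by-time F test asks whether the group difference varies in any way across four visits. It gives neither a direction nor a visit, so the short-term and long-term effects are left to unspecified follow-up comparisons.
- **Incomplete participants are lost.** Classical repeated-measures ANOVA needs a full row per participant. With a quarter expected to drop out, people who have an immediate post-treatment value but miss a later visit contribute nothing. The result is a comparison of completers, which is less robust than a likelihood-based analysis when drop-out depends on values already observed.

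**Working it through.** **The plan's own figure.** Take 1.08 as a standardised two-group difference and assume two-sided 5% and 90% power. The normal approximation gives 2 × (1.960 + 1.282)² / 1.08² = 18.02, so 19 per arm. The exact t calculation gives 20 per arm (power 91.4%), so the stated 40 is reproduced. It belongs to a single two-group comparison, not to an interaction test. For attrition, 40 × 1.25 = 50 as stated, and 60 × 0.75 = 45 completers from the planned enrolment.

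**Degrees of freedom.** (2 − 1) × (4 − 1) = 3.

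**Assumptions not in the protocol.** Visit correlation ρ of 0.5 or 0.7, equal at all lags; cumulative missingness of 5%, 15% and 25% at the three post-treatment visits, completely at random; two-sided 5%. Then 60 × 0.95 = 57 participants have an immediate value and 45 are complete, so 57 − 45 = 12 immediate values would be discarded.

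**Closed form, interaction in completers** (n = 22.5 per arm). With δ the group difference at each visit in SD units, λ = (n/2) × Σ(δ − mean δ)² / (1 − ρ), on 3 and 3(2n − 2) = 129 df.

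- Constant effect d after baseline: the sum is 0.75d². For d = 0.6 and ρ = 0.5, λ = 11.25 × 0.27 / 0.5 = 6.08, power 51%. For ρ = 0.7, λ = 10.1, power 75%.
- Same pattern at d = 1.08: the sum is 0.875. λ = 19.7, power 97% (ρ = 0.5); λ = 32.8, power above 99% (ρ = 0.7).
- Waning 1.08, 0.72, 0.36: the sum is 0.648. λ = 14.6, power 90% (ρ = 0.5); λ = 24.3, power 99% (ρ = 0.7).

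**Closed form, baseline-adjusted difference at one visit.** Noncentrality = d × √(n/2) / √(1 − ρ²), on 2n − 3 df. For d = 0.6:

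- Immediate visit (n = 28.5 per arm): 2.62, power 73% (ρ = 0.5); 3.17, power 88% (ρ = 0.7).
- 3 months (n = 22.5 per arm): 2.32, power 62% (ρ = 0.5); 2.82, power 79% (ρ = 0.7).

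**Simulation**, 30 per arm, a few thousand trials per setting (simulation error about one percentage point). Each cell gives power for ρ = 0.5 / 0.7.

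| Effect at the three post visits (SD) | Interaction, completers | Adjusted, immediate visit | Adjusted, 3 months |
|---|---|---|---|
| 0.6, 0.6, 0.6 | 52% / 75% | 71% / 87% | 61% / 76% |
| 0.6, 0.4, 0.2 (waning) | 39% / 60% | 72% / 87% | not tabulated |
| 0.2, 0.4, 0.6 (late-building) | 40% / 60% | 13% / 17% | 61% / 76% (same as row 1) |
| 1.08, 1.08, 1.08 | 96% / 100% | 99% / 100% | not tabulated |
| 1.08, 0.72, 0.36 (waning) | about 91% / 99% | not tabulated | not tabulated |

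Type I error was about 5% for both the interaction and the adjusted contrast.

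**Where the gain comes from.** For a constant 0.6 SD and ρ = 0.5, an adjusted contrast on the mean of the post-treatment visits has 86% power in completers alone and 89% using all available visits, against 51% for the interaction. Most of the gain comes from the focused, baseline-adjusted contrast and a smaller part from keeping incomplete participants.

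**The case against.** The strongest reply is that the protocol's two sentences do not state the factors, the deciding test or a missing-data rule. Deletion of incomplete participants is a property of the classical method, not a rule the protocol writes down, and an unseen analysis plan could add a rule. That is fair, and it is why the completer point is stated only for the classical form. It does not remove the point about the method: no other two-way reading fits two arms and four visits.

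Second, a reader might infer that the trial is underpowered. The documents do not support that. At the protocol's own 1.08 the interaction keeps roughly 90% power or more in every setting tabulated, and 60 enrolled against 40 required already absorbs the loss of numbers. The 0.6 SD is an assumption below the design value. It is plausible because, by the protocol's own Background, 1.08 comes from six acute patients whose gains may partly reflect spontaneous recovery, whereas this trial enrols people at least 6 months after stroke.

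Third, the comparison depends on the visit. If the effect builds late, the immediate-visit contrast does much worse than the omnibus test. This stands, and it is why the visit must be chosen in advance.

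Fourth, a reader might take the open follow-up comparisons as a plan to infer efficacy from within-arm change, or read the ANOVA's label as a design error. The protocol proposes no within-arm inference, and the label is terminology. Neither is part of this point.

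**Conclusion.** The point holds as one of efficiency, use of partial follow-up, robustness to drop-out and a direct answer to the aim. It should be fixed. It is not one of validity: the planned test holds its level.

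For a constant 0.6 SD, the gain over the interaction is about 12 to 19 percentage points at the immediate visit (87 − 75 and 71 − 52) and about 1 to 9 at 3 months (76 − 75 and 61 − 52). At 1.08 it is small. These figures rest on equal correlation between visits, the assumed missingness pattern and drop-out completely at random. The adjusted contrast was computed one visit at a time; the full mixed model recommended below was not itself simulated. Bias from differential drop-out was not quantified either. A reader might conclude that the completer analysis would be biased, but the documents show only that it would be more exposed to bias.

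**What to change.** Replace the ANOVA sentence with a linear mixed model for repeated measures, fitted to all randomised participants, as randomised, who have any post-treatment value:

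- **Outcomes:** the immediate, 1-month and 3-month values.
- **Terms:** group, visit, group-by-visit, baseline value of the same measure, and baseline-by-visit.
- **Covariance:** unstructured, with Kenward-Roger degrees of freedom as one suitable choice.
- **Conclusion:** based on the adjusted group difference at one primary visit, named before unblinding. The other two visits are reported as adjusted between-group contrasts with confidence intervals, so that the short-term and long-term effects are each estimated.

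The cost is a change of wording and slightly more analysis work, with no extra participants or assessments. The downside is that a single named visit has less power than the omnibus test if the effect arises at a different visit, so the choice of visit needs a stated rationale.
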